### Randomization

The clinics will be randomized without repeating by a Data Scientist (not involved in the trial) using a computer system. Each GP clinic will be allocated randomly to one of three equal-sized arms: two intervention arms and a control arm by Data Scientist.

The clinics from the intervention arms will find out that they are enrolled when they receive the letters with interventions. The letters will be sent simultaneously. The control arm will only use usual care and has no intervention.

### Blinding

Participants in this trial will be anonymized rather than blinded. Because of the nature of the interventions, it is not possible to blind the GP participants in the clinics. Outcome assessment will not be blinded as the researchers will be aware of practice arm allocation. The Data Scientist will not be blinded, because she will be independent of the research team.

### Interventions

The educational intervention program will consist of providing GPs in two intervention arms with a COPD management checklist (Additional file 1).

In the first intervention arm, the checklist will be delivered at the beginning of the study (March 2020); in the second arm, it will be delivered at the beginning of the study and repeated after 6 months. Clinics that are randomized to the control arm will not receive the COPD management checklist, and GPs will treat all patients according to standard care.

The checklist was developed by authors on the basis of GOLD guidelines [20] and the 2015 Physician Quality Reporting System (PQRS) Implementation Guide Centers for Medicare & Medicaid Services [21].

### Outcomes

*The primary outcome of the study* will be the effect of the interventions on the proportion of “hospitalization with the J-44 code as a main reason for admission,” and the proportion of deaths of elderly COPD patients, registered within practices after 1 year.

*Primary outcome at the patient level* will be assessed as the proportion of cases between the three arms (intervention 1, intervention 2 and control) at the end of the 1-year study period. Proportion of cases (event rates) of binary variables of exacerbation outcome will be assessed based on “hospitalization with the J-44 code as a main reason for admission,” and the proportion of deaths of elderly COPD patients.

The effect of the educational intervention will be evaluated using logistic 2-level regression analysis, based on odds ratios (OR) and 95% confidence limits.

We will examine the association between intervention and COPD exacerbation, using a case-control approach. Cases will be selected among COPD exacerbation after 1 year. Control subjects will be selected among COPD patients.

*Secondary outcome at the patient level* will be the proportion of the control and intervention arms regarding the specific short- and long-acting drugs prescribed after 1 year.

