## Methods/design

### Study setting

Eighty-four GP clinics in the Lodz voivodship in Poland will be identified at baseline using data from the National Health Fund’s (*Narodowy Fundusz Zdrowia*, NFZ) electronic medical records (EHR). They will be randomly selected using the following criteria: clinics with at least 30 patients per clinic, aged 65 years and older with COPD. Patients with COPD will be identified by the ICD-10 code J-44 in NFZ electronic medical records; exacerbations will be defined as cases hospitalized with the J-44 code as the main reason for admission.

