**Fig. 1 Fig1:**
[figure not shown]
The schedule of the study

The endline data for the clinic and patients will be collected after 1 year. We will consider additional data collections from other time points based on the development of the COVID situation.

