### Statistical methods for analysis

Post-intervention analysis will be performed.

The following data will be analyzed in the post-intervention patients: hospitalization with the J-44 code as the main reason for admission, and use of medication. The analysis will be based on multilevel regression models.

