#### Test statistics for primary outcome and dependent variable

The effect of the educational interventions will be evaluated using two-level logistic regression models with a dependent binary variable (case-control, cross-sectional analysis), with patients nested within practices.

Data regarding hospitalization will be collected directly from patient electronic health records held by the National Health Fund (NHF—the state health insurance system). Patients registering exacerbation, defined as “hospitalization of patients with the J-44 as a main reason for admission,” will be classed as cases. Control subjects will be collected from electronic health records held by the NHF, defined as COPD (J-44), age over 65, with low treatment cost, and no constantly reimbursed drugs. Data will be collected after the 1-year study period (cross-sectional) within the Lodz voivodeship.

Descriptive statistics and logistic regression will be employed. The level of statistical significance will be *p* < 0.05.

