## Trial status

The trial is currently in the interventions phase.

ClinicalTrial.gov identifier: NCT04301505. Registered on 10 March 2020, https://clinicaltrials.gov/ct2/show/NCT04301505

Protocol Version 9: 16 January 2021.

Date recruitment began: March 2020.

Estimate of the date when recruitment will be completed: March 2021.

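### The J-44 patient cohort is not fixed before the checklist letters go out, so the intervention could change who is counted in the primary outcome

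*Protocol article*

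**What the plan says.** Clinics are settled before the intervention. Under Study setting, "Eighty-four GP clinics in the Lodz voivodship in Poland will be identified at baseline", and the selection criterion is "clinics with at least 30 patients per clinic, aged 65 years and older with COPD". Patients are recognised by the J-44 code in the National Health Fund (NFZ) records. No date is given by which the code must be present.

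The wording on the analysed population then moves to the end of the year:

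- Outcomes names two primary outcomes, J-44 admission and death, as proportions "registered within practices after 1 year".
- Statistical methods for analysis says "The following data will be analyzed in the post-intervention patients".
- Test statistics for primary outcome and dependent variable describes a case-control, cross-sectional model and adds: "Data will be collected after the 1-year study period (cross-sectional) within the Lodz voivodeship".
- The same section limits the non-cases to J-44 patients over 65 whose treatment is cheap and who take no regularly reimbursed medicines.

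Blinding states that the GPs cannot be blinded. Interventions states that two arms receive a COPD management checklist, once or twice, and that the control arm receives none. Discussion lists the accuracy of COPD coding among the main limitations.

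**The concern.** In a cluster trial, randomisation protects the comparison of patients only if membership of each cluster is decided before allocation can affect it. Here the qualifying diagnosis may be assigned by the same clinicians who receive the intervention and know that they have it. If a COPD checklist leads some of them to code more patients, probably milder ones, the denominator grows in the checklist arms only. The admission proportion then falls without one admission being prevented. Adjustment for age and gender, the only patient covariates listed, would not remove this. The second arm gets the checklist twice, so drift in coding could also imitate the graded effect that the sample size assumes.

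Two further points follow from the same gap. A list of patients still registered at the end of the year cannot supply a proportion of deaths. And a comparison set restricted to low-cost patients without regular reimbursed drugs is not the full J-44 list on which an event rate of 0.105 is meaningful.

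**Working it through.** **Inputs from Sample size.** Control event rate 0.105; SD 0.306; reductions of 25% and 50%; two-sided alpha 0.05; power 80%; ICC 0.01; 28 clinics per arm with 30 patients each.

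**The plan's own figure.** The arm means are 0.105, 0.105 × 0.75 = 0.07875 and 0.105 × 0.50 = 0.0525. One-way ANOVA power from the noncentral F distribution gives 656 patients per arm. The design effect is 1 + (30 − 1) × 0.01 = 1.29. Then 656 × 1.29 = 846 per arm, which is 28.2 clinics, or 2,539 patients in total. The stated 84 clinics and 2,520 patients are reproduced closely; power at 2,520 is 79.7%. The sample size is therefore not at issue.

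**Effect of extra coding with no true effect.** Let e be the extra J-44 patients in a checklist arm as a fraction of the original list, and r their admission rate. The observed proportion is (0.105 + e × r) / (1 + e). The documents give neither e nor r; the values below are assumptions.

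| e | r | Observed proportion | Spurious relative reduction |
|---|---|---|---|
| 0.10 | 0.05 | 0.110 / 1.10 = 0.1000 | 4.8% |
| 0.10 | 0 | 0.105 / 1.10 = 0.0955 | 9.1% |
| 0.20 | 0.05 | 0.115 / 1.20 = 0.0958 | 8.7% |
| 0.20 | 0 | 0.105 / 1.20 = 0.0875 | 16.7% |

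To reproduce the whole 25% effect with r = 0 requires 1 / (1 + e) = 0.75, so e is about 0.33.

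**Chance of a false benefit.** Take one comparison of a checklist arm with control, 840 / 1.29 = 651 effective patients per arm, SD 0.306 and two-sided alpha 0.05. Let the new patients have between none and half of the 0.105 rate. The chance of a nominally significant result in favour of the checklist is about 5–8% at e = 0.10 and 7–18% at e = 0.20, against 2.5% in that direction without bias.

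**If the denominator were survivors only.** Let d be one-year mortality and k the admission risk of those who die relative to survivors, both assumed. The survivor rate is 0.105 / (1 − d + d × k). With d = 0.03 and k = 2 it is 0.105 / 1.03 = 0.102; with d = 0.10 and k = 4 it is 0.105 / 1.30 = 0.081. This shifts the level in every arm, and distorts the comparison only as far as the loss differs between arms.

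**The case against.** The strongest reply is that the text is loose rather than wrong. The phrase in Outcomes can describe admissions and deaths recorded over the year as easily as patients on a list. Extracting data after follow-up is normal in a records-based trial. Observation period states that the data cover March 2020 to February 2021, so "The endline data for the clinic and patients will be collected after 1 year" says when the extract is made, not who is in it. An article may also leave an exact index date to the full protocol.

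Most of this stands, and it rules out three stronger readings.

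- A reader might infer that patients who died or left are dropped from their own outcome. The documents do not say so. Death is a primary outcome and a listed study variable, so the evident intention is to count it. On patients who change practice the text is silent.
- A reader might infer that the checklist does change coding. It is described as a management tool, and its content (Additional file 1) is not shown. The mechanism is plausible, not demonstrated.
- A reader might take "Estimate of the date when recruitment will be completed: March 2021" as proof that patients enter after the observation year. That status line does not say whether clinics or patients are meant, and it adds little.

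What the reply does not remove is that the article goes beyond leaving a date out. It does describe a population, in post-intervention and cross-sectional terms, and it adds a restricted comparison set. Someone who followed that text could build the denominator after the checklist had acted.

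**Conclusion.** The point holds in this form: clinics are fixed at baseline, patients are not, and the analysed population is described in terms that allow coding by unblinded GPs to alter it. Read as an end-of-year list, the Outcomes wording also contradicts the death outcome; read as recorded events, it does not.

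The possible size is a spurious 5–17% relative reduction in J-44 admissions, against an assumed 25%. It rests entirely on assumed inputs: 10–20% extra coded patients, confined to the checklist arms, with an admission rate of 0–0.05. It is an illustrative range and not an estimate. With no extra coding there is no bias from this source.

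**What to change.** Replace the post-intervention population and the cross-sectional case-control selection with a cohort fixed in advance:

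- **Membership:** all patients aged 65 and older with J-44 recorded in a randomised clinic before the first letters were sent.
- **Follow-up:** admissions, deaths and drugs counted over 12 months for every member, including those who die and, as far as NFZ records allow, those who change practice.
- **Analysis:** by the allocation of the baseline clinic.
- **Comparison set:** for this comparison, remove the low-cost and no-reimbursed-drugs restriction on non-cases, since it conflicts with a full-list denominator.
- **Age:** use 65 and older throughout; Study setting has this, while the definition of control subjects has over 65.
- **New codes:** report patients first coded J-44 during the year by arm, as a descriptive group. This also shows whether coding drifted.

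The cost is mainly wording and a look-back date in the same NFZ extract. Extraction was planned for March to June 2021, after the protocol version of 16 January 2021. The sample size of 84 clinics and 2,520 patients is unaffected if the 30 per clinic are counted at baseline. There are two limits. Newly coded patients leave the primary analysis, and following patients across practices needs a link in depersonalised data that the article neither confirms nor excludes.

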### Data collection methods

Patient data will be obtained from Big Data databases, such as the patient electronic health record system from the National Health Fund (NFZ).

### Data management

Depersonalized data will be obtained and subjected to quality control and cleaning.

The structure of the obtained data will be hierarchical. Individual patient data will be anonymized. Patients will be nested within PC clinics. The approach to missing data will be determined once the data is obtained.

Big Data cleansing process will be performed according to SAS Data Management Methodology. This methodology covers a step-by-step process, and it covers tasks such as data management, data quality, data integration, data migrations, and master data management.

Study variables: demographic and characteristics will include age; gender; residence code; “hospitalized, with the J-44 code as the main reason for admission”; death; specific short- and long-acting medication prescribed; and number of GPs.

### Statistical methods for analysis

Post-intervention analysis will be performed.

The following data will be analyzed in the post-intervention patients: hospitalization with the J-44 code as the main reason for admission, and use of medication. The analysis will be based on multilevel regression models.

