### Observation period

The study will include data for 1 year, from March 2020 until February 2021. Data extraction and analysis will take place from March until June 2021 (see Fig. 1).

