### Sample size

A minimum number of 84 GP clinics with at least 30 J-44 patients per clinic is required to provide a sufficient sample size for a three-arm cluster randomized controlled trial: 84 clusters and at least 2520 subjects are needed (28 clusters in each study arm) to detect a difference of 0.026 between mean event rates of hospitalization with ICD-10 code J-44 as the main reason for admission. This assumes a 25% reduction in total number of events after the intervention in the first arm (receiving checklist once) and 50% reduction in total number of events after the interventions in the second arm (receiving checklist twice) compared to the control group not receiving any intervention (standard care). It is also assumed the tests will have 80% power, a two-tailed alpha of 0.05, and intra-cluster correlation of 0.01.

Data collected from electronic health records in 2016 indicate that the mean event rate of “hospitalized with ICD-10 code J-44 as the main reason for admission” in the control group is 0.105, and the standard deviation is 0.306. The unadjusted sample size was calculated for differences between three means for one-way ANOVA.

To compare the individuals hospitalized with the J-44 code in the three arms after 1 year, the difference between the mean event rates of the three groups was calculated according to Donner and Klar [16].

A standard sample size formula was used to calculate the initial unadjusted sample size requirements, followed by appropriate adjustment for clustering by general practice according to Campbell et al. [17], with expected small clustering effect (ICC = 0.01) [18, 19].

To prevent loss to follow-up among practices/participants, an enlarged overall sample size will be deemed appropriate to ensure adequate power.

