#### Categorical predictors

Educational interventions after 1 year in two arms, and an arm with standard care (control), age and gender.

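### The stated model uses trial-year data only and omits prior-year J-44 admission: the comparison is valid, but a modest, assumption-dependent gain in precision is forgone

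*Protocol article*

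**What the plan says.** Four sections of the protocol article together describe an analysis without a baseline outcome.

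- Observation period: "The study will include data for 1 year, from March 2020 until February 2021".
- Statistical methods for analysis: "Post-intervention analysis will be performed", and then "The following data will be analyzed in the post-intervention patients: hospitalization with the J-44 code as the main reason for admission, and use of medication".
- Categorical predictors: "Educational interventions after 1 year in two arms, and an arm with standard care (control), age and gender".
- Test statistics for primary outcome: "two-level logistic regression models with a dependent binary variable (case-control, cross-sectional analysis), with patients nested within practices".

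The variable list under Data management names J-44 hospitalization once, with no prior-period version. Randomization describes allocation of clinics to three arms of equal size and mentions no stratification or balancing.

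Elsewhere the article shows that earlier records can be reached. Under Study setting, the clinics "will be identified at baseline using data from the National Health Fund", and J-44 patients are identified in the same records. Under Sample size, the planning rate is historical: "Data collected from electronic health records in 2016 indicate that the mean event rate of" J-44 hospitalization in the control group is 0.105.

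**The concern.** Whether a patient was admitted for COPD in the previous year is the outcome's own baseline value and a natural covariate for admission in the trial year. Here it would probably cost one more query to a database already in use. Leaving it out means that variation between patients and clinics which could be explained stays in the error term. It also means that a chance difference in underlying admission risk between arms, each of only 28 clinics, is corrected neither by design nor by analysis.

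What is at stake is efficiency and the credibility of a single realised allocation. Bias and type I error are not at stake.

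**Working it through.** **Inputs (Sample size section).** Control rate 0.105, SD 0.306, ICC 0.01, 28 clinics per arm with 30 patients each (84 clinics, 2520 patients), 80% power, two-sided alpha 0.05, difference 0.026, reductions of 25% and 50%.

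**1. The plan's own figure.** The reductions give means of 0.105, 0.07875 and 0.0525. The effect size is f = sqrt((2 × 0.02625²)/3)/0.306 = 0.0700. A one-way ANOVA at 80% power needs 656 patients per arm. The design effect is 1 + 29 × 0.01 = 1.29, so the total is 3 × 656 × 1.29 = 2539. With steps of exactly 0.026, it is 3 × 669 × 1.29 = 2589. Both are within 3% of 2520, so the stated size reproduces. At 28 × 30 per arm (effective n = 840/1.29 = 651), power is 79.7% and 78.9% respectively. There is no slack.

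**2. Gain from adjustment, simple form.** On a linear scale, a baseline covariate correlated r with the outcome multiplies the variance by 1 − r². The documents give no r, so 0.2-0.3 is assumed.

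- r = 0.2: 0.04 of variance removed; 0.04 × 84 = 3.4 clinics.
- r = 0.3: 0.09 of variance removed; 0.09 × 84 = 7.6 clinics.

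To judge whether that range is plausible, suppose 10.5% are admitted in each year. A prior admission that doubles the risk gives a correlation of 0.095; threefold gives 0.174, fourfold 0.240 and fivefold 0.296. The assumed range therefore needs a strong association.

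**3. Sensitivity with a clinic level.** Let rs be the patient-level and rc the clinic-level year-to-year correlation, both assumed. Then r = [30 × 0.01 × rc + 0.99 × rs]/1.29 = 0.233 rc + 0.767 rs.

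| rs | rc | r | 1 − r² | Clinics saved (of 84) | ANOVA power |
|---|---|---|---|---|---|
| 0.1 | 0 | 0.077 | 0.994 | 0.5 | 80.0% |
| 0.1 | 0.5 | 0.193 | 0.963 | 3.1 | 81.3% |
| 0.2 | 0.5 | 0.270 | 0.927 | 6.1 | 82.8% |
| 0.3 | 0.5 | 0.347 | 0.880 | 10.1 | 84.8% |
| 0.4 | 0.8 | 0.493 | 0.757 | 20.4 | 90.0% |

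Across these rows, power for single checklist versus control rises from 37% unadjusted to between 38% and 47%. Adjustment helps, but it does not repair that comparison.

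**4. Size of a chance imbalance in underlying risk.** The outcome variance is 0.105 × 0.895 = 0.094. At ICC 0.01, the SE of the difference between two arms in underlying clinic risk is sqrt(2 × 0.01 × 0.094/28) = 0.0082, a 95% range of ±0.016. If a share s of the within-clinic variance is stable patient risk, the SE is sqrt(2 × [0.01 × 0.094/28 + s × 0.99 × 0.094/840]). This gives 0.0106 for s = 0.2 and 0.0116 for s = 0.3, or ±0.021 to ±0.023. These values are below the 0.026 sought, though not negligible beside it.

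**5. Carry-over.** An observed baseline difference of 0.026 would pass r × 0.026 into the unadjusted comparison: 0.005 at r = 0.2 and 0.008 at r = 0.3.

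**The case against.** The strongest reply is that nothing here is an error. A post-only comparison of randomised arms is unbiased over randomisations, its standard error already includes chance imbalance, and the sample size does not count on adjustment. That stands, and it limits the point to an improvement.

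A reader might infer something stronger. The SE of the difference in observed one-year proportions between two arms is 0.306 × sqrt(2 × 1.29/840) = 0.017, a 95% range of ±0.033, which seems to show that the arms can easily differ at baseline by more than 0.026. The documents do not support that for underlying risk. The figure is mostly binomial noise in an observed proportion and is the same variance the sample size already allows for. Step 4 gives the relevant quantity, and it is smaller than 0.026.

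Four further replies stand in part.

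- The predictor list does not say it is complete, and an analysis plan could add covariates. However, the one-year data window and the post-intervention, cross-sectional description are stated choices, not omitted detail. The coding of age, and the absence from the model of listed fields such as residence code "and number of GPs", are minor and largely a matter for an analysis plan.
- Availability is inferred. The article does not name the National Health Fund as the source of the 2016 rate, and it does not say whether anonymised patients can be linked across years.
- The r² calculation is linear. In a logistic model a prognostic covariate changes the conditional odds ratio and need not shrink its standard error; the benefit appears as power.
- The outcome analysis is also described as case-control, with controls selected partly on treatment cost. Prior admission is plausibly related to that selection, so adding it to such a sample could adjust for how controls were chosen.

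**Conclusion.** The point holds as a modest, inexpensive improvement. The stated analysis is valid but leaves out a covariate that very probably exists in the source database, while power is about 79-80%. At an assumed correlation of 0.2-0.3 the gain is about 4-9% of outcome variance, or roughly 3-8 of 84 clinics. It is under one clinic if the correlation is weak, and COVID, which the Discussion names as a possible distortion, could weaken the link between 2019-20 and the trial year. The gain would be larger if clinic rates are stable from year to year.

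The conclusion rests on three assumptions: that prior-year admissions can be linked to patients, that the correlation is in the assumed range, and that the analysis is run on a cohort fixed at baseline. The article's remarks about considering other time points are conditional, concern COVID, and do not place prior admission in the model.

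**What to change.** Before the March to June 2021 extraction:

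1. Define the analysis cohort as J-44 patients aged 65 and older registered in the randomised clinics at baseline.
2. Request their J-44 main-reason admissions for March 2019 to February 2020, linked before the data are anonymised.
3. Prespecify two covariates in the two-level logistic model: the patient's prior-year J-44 admission (yes/no) and the clinic's prior-year admission proportion. Enter age as continuous.
4. Fit this model to the full cohort, not to a sample whose controls are selected on cost.

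Timing matters: the covariates should be fixed before results are seen, because outcome assessment is not blinded, and linkage may be impossible once anonymised data have been delivered.

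The cost is one additional linked extract and no patient contact. The cohort definition must be settled first, so the change is more than one sentence about the model. The odds ratio becomes conditional on the added covariates, and its interpretation shifts slightly.
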